## Abstract

**Background:**

Germany faces increasing challenges in primary care due to demographic change, workforce shortages, and the growing prevalence of chronic conditions. Integrating nursing professionals into primary care teams may improve continuity, comprehensiveness, and efficiency of care, but evidence for the German setting remains limited. The PRIMA project (DRKS00039104) implements a new care model that transforms general practices into multiprofessional primary care centers integrating specially trained nursing professionals. The objective is a productivity- and quality-oriented reorganization of care for patients with chronic diseases. The intervention targets patients with high-risk chronic diseases. Core elements include extended nursing services, subsidiary task allocation within the practice team, structured organizational development, and optional use of a medical triage software.

**Methods:**

Effectiveness and health-economic outcomes are evaluated in a prospective, quasi-experimental, controlled study under real-world conditions. The intervention group includes patients from 20 participating practices; the control group is matched using routine claims data. The primary endpoint is the number of ambulatory care–sensitive emergency cases after 12 months, analyzed intention-to-treat. Secondary outcomes include healthcare utilization, mortality, continuity, and coordination of care. Statistical analyses will account for confounding and clustering at practice and patient level. The health economic evaluation will estimate incremental cost-effectiveness ratios based on ambulatory and total healthcare costs. A parallel process evaluation uses longitudinal mixed-methods. It comprises interviews, activity logs and focus groups, and surveys among patients, their relatives, practice teams and collaborators. Key aspects assessed include implementation facilitators and barriers, organizational development and interprofessional collaboration, nurse role development, and patient quality of life and treatment satisfaction.

**Discussion:**

Findings are highly relevant for strengthening primary care in Germany and internationally, where multidisciplinary primary care centers are increasingly promoted. If successful, the intervention could reduce emergencies and improve patient outcomes, serving as a scalable model and informing policy and reimbursement strategies.

## Introduction

The provision of primary care by general practitioners (GPs) and their teams in Germany is already at risk in many regions and is expected to become a central challenge over the next two decades due to demographic change and decreasing workforce in this care sector [1,2]. The consequences affect both the individual patient – whose care may no longer be adequately ensured – and the healthcare system as a whole – as inappropriate utilization of specialist care, emergency departments, and avoidable hospitalizations are likely to increase.

Multiple strategies targeting different levels of the healthcare system, including medical education, postgraduate training, and incentives for practice establishment, have been introduced to strengthen the workforce within primary care. Nevertheless, demographic developments, increasing complexity of care, and limited physician availability suggest that expanding the physician workforce alone will not adequately address future primary care needs [3]. This particularly concerns continuity of care, which is essential for patients with chronic conditions and multimorbidity, as well as increasing needs related to counselling, prevention, and self-management support [4]. Strengthening organizational structures and workflows within primary care practices is necessary to ensure that limited physician capacity is reserved for activities requiring medical decision-making and clinical expertise. Tasks that do not require physician qualification may be delegated to adequately trained non-physician personnel or streamlined through process redesign and technological solutions. One internationally established approach is the integration of (academically trained) nursing professionals into primary care teams [5–7].

Traditionally, German primary care teams consist of general practitioners and medical assistants (“Medizinische Fachangestellte”). While nurses, particularly Advanced Practice Nurses (APNs) are well established in primary care internationally, they have so far only played a marginal role within German general practice teams. Unlike many international healthcare systems, nursing in Germany has traditionally been rooted in non-academic vocational training, and the academic institutionalization of nursing science is still evolving. Furthermore, legal, professional, and reimbursement regulations governing the integration of academically trained nurses into primary care settings remain fragmented and incompletely defined. This has mainly been attributed to three structural factors: (1) a traditionally physician-centered healthcare system based on delegation rather than substitution of medical tasks, (2) a predominantly physician-oriented reimbursement system in ambulatory care, and (3) historically developed professional structures in which physician practices are primarily staffed by medical assistants. In recent years, expanded qualification pathways for non-physician practice staff, including VERAH (“Versorgungsassistentin in der Hausarztpraxis”, GP-Practice Assistant), NäPA (“Nichtärztliche Praxisassistenz”, Non-medical Practice Assistant), physician assistants and academic programs such as Primary Care Management, have contributed to changes in the composition and scope of German general practice teams. Nevertheless, nurses, and their profession-specific competencies continue to play a minor role within German general practice teams, even when employed in practices, where they frequently work in roles comparable to those of medical assistants. Evidence from primary care settings suggests that the involvement of APNs is associated with outcomes comparable or superior to traditional physician-led care regarding safety, clinical outcomes, costs, and patient satisfaction, although resource utilization may differ between models of care [6,8–13]. Heterogeneous findings regarding efficiency and costs have partly been attributed to longer consultation times and more frequent follow-up visits, which may nevertheless contribute to improved disease management and reduced hospitalization rates [7,10]. Empirical evidence regarding the integration of nurses in general, and APNs specifically, into German general practice teams remains limited. Nevertheless, recent third-party funding projects have indicated that the inclusion of academically trained nurses in primary care teams may improve quality of care, patient-centeredness, and relieve physician workload [14,15]. While patients generally report high acceptance of transferring selected care tasks to nurses, several barriers remain, including unclear legal frameworks, insufficient role clarity, and unresolved reimbursement structures [6,16].

Against this background, the PRIMA project aims to implement a novel model of care by transforming general practices into multiprofessional primary care centers (PRIMA), in which nurses, either academic or non-academic and in the following referred to as “PRIMA nurse” (PN), are integrated into general practice teams. This model of care utilizes the inherent competencies of an experienced nurse to enhance continuity, comprehensiveness and subsidiarity of care and aims at enabling an efficient allocation of tasks according to professional competencies present in the practice team (e.g., medical, administrative and nursing competencies). Within this care model, activities of the PN are classified into seven predefined interventions for patients with chronic conditions that extend beyond routine care and were developed based on the Chronic Care Model (CCM) [17]. Based on this, a remuneration system is introduced that supports the sustainable implementation of these structural and process changes. PRIMA targets patients with chronic conditions, especially those at high risk of decompensation or signs of instability. As demographic change and the increasing prevalence of chronic diseases pose significant challenges to care delivery, these patients have been shown to benefit from nurse-integrated primary care teams [18].

The study evaluates the effectiveness, implementation, and economic implications of the new care model (NCM) at micro-, meso-, and macro-levels. At the micro-level (patient level), the study examines whether the NCM improves predefined primary and secondary outcomes compared with usual care. It is hypothesized that the intervention supports appropriate treatment, facilitates early identification and management of deterioration and complications, strengthens patient self-management and caregiver involvement, and thereby reduces ambulatory care-sensitive emergency cases (ASE) while improving patient-relevant outcomes. In addition, patient and caregiver perspectives on the intervention will be assessed.

At the meso-level (practice level), the study investigates whether the NCM can be implemented as intended. Furthermore, the implementation process, including facilitators and barriers to implementation as well as effects on workflows and interprofessional collaboration will be evaluated.

At the macro-level (health system level), the study assesses the costs and cost-effectiveness of the NCM from the perspectives of healthcare payers and participating primary care practices. It is hypothesized that the intervention may reduce healthcare expenditures through fewer ASE and more efficient utilization of healthcare services, while changes in practice organization and reimbursement structures may also generate economic benefits for participating practices.

## Materials and methods

### Patient and public involvement

Stakeholder involvement was incorporated throughout the development and implementation of the project. During the conceptual phase, two advisory meetings were conducted with a physician advisory board that included representatives of the German Association of General Practitioners (Hausärztinnen- und Hausärzteverband) and MEDI, a large interdisciplinary network representing office-based physicians and psychotherapists in Germany. During the implementation phase, the project is supported by a scientific advisory board comprising representatives of the German Nurses Association (DBfK), nursing scientists, an APN, a patient representative from LAG-Selbsthilfe, a regional umbrella organization for patient self-help groups, a representative of the German Association of General Practitioners, and a GP working in a primary care unit in Austria. The advisory board meets annually and provides independent advice to the project team regarding the implementation and evaluation of the intervention.

### Aim

The aim of PRIMA is to develop primary care teams in general practices into multiprofessional primary care teams by integrating PNs with specific tasks. Based on the CCM, a NCM optimizing the management of patients with chronic conditions will be implemented [17].

### Design

The PRIMA study is a non-randomized, controlled, cluster-based, quasi-experimental intervention study. The study is designed as a superiority trial, aiming to demonstrate improved outcomes of a multiprofessional primary care model compared to usual care. The intervention group (IG) consists of the patients recruited from the 20 participating GP practices. The control group (CG) will be established through matching based on routine data. In addition to the effectiveness evaluation, a mixed-methods process evaluation (PE) based on the Consolidated Framework for Implementation Research (CFIR) will be conducted to assess implementation processes, contextual factors, and intervention fidelity [19]. The PE includes team members from the participating practices, participating patients and their relatives as well as collaborators. For both quantitative and qualitative data, a longitudinal approach is applied, the latter reflected in qualitative case studies encompassing interviews, qualitative activity logs and focus groups. Repeated data collection will enable the investigation of evolving implementation processes, barriers, and facilitators across different stages of implementation and give insight in the implementation, adaption and integration of the intervention into routine practice over time.

### Setting

The trial is conducted in the German ambulatory primary care setting, namely in 20 general practices located in the federal state of Baden-Württemberg, Germany. The participating practices provide routine outpatient care services within the German statutory health insurance (SHI) system.

The target population of PRIMA are patients with a chronic condition as defined within the German statutory healthcare system. Within this system, a chronic condition can be identified on the Uniform Value Scale (EBM), which is jointly developed by the National Association of SHI Physicians and the National Association of SHI Funds. The conceptual basis of this definition is derived from German social law, in particular the definition of “severe chronic disease” according to § 62 of the Social Code Book V, and its specification by the Federal Joint Committee [20]. Within the EBM framework, chronic illness is operationalized for billing purposes in the billing code chronic care reimbursement (“Chronikerpauschale”: 03220/03221) [21]. Patients are classified as chronically ill if they have a documented, continuous need for medical care due to the same confirmed diagnosis over a period of at least 12 months. This requirement is typically operationalized through repeated physician–patient contacts across multiple quarters rather than pre-defined clinical criteria, usually in at least three out of four consecutive quarters, reflecting sustained utilization of care. In addition, an ongoing need for treatment must be present. Thus, the EBM-based definition represents an administrative and utilization-based proxy for chronic illness, grounded in legal and regulatory frameworks rather than purely epidemiological or clinical definitions. Patients eligible for inclusion in the study were identified from the population of individuals receiving the chronic care reimbursement billing code (“Chronikerpauschale”), which served as the source population for the study. Additional clinical eligibility criteria were subsequently applied to identify patients with an increased risk of care instability or decompensation in a step-wise approach.

### Sample size calculation

For the sample size and power calculation, a baseline rate of 0.20 ASE per patient per year is assumed. In the general population, ASE rates range between 4% and 8% [22]. As the study population consists of patients with chronic conditions selected based on clinical judgement and expected to benefit from enhanced care, a higher baseline rate is expected. Based on published evidence suggesting a 20–40% reduction in ASEs through improved ambulatory care [23], a conservative effect size of 15% is applied.

The study follows a parallel cluster design with 20 practices per arm and approximately 112 patients per practice. This accounts for an anticipated dropout of 20% at practice level and 10% at patient level. The design includes 12 months of pre- and 12 months of post-intervention observation [24]. An intra-cluster correlation coefficient (ICC) of 0.01 is used. Under these assumptions and a two-sided alpha of 5%, the study achieves a statistical power of 82% to detect a 15% reduction in ASE rates.

The PE within PRIMA does not assess a primary endpoint of the study. Therefore, no separate sample size calculation was required for the PE. Instead, the sample size of the PE is determined by the total population of all participant groups included in the PRIMA study and by the methodological approach chosen within the PE sub-projects. For the questionnaire-based quantitative PE, all patients included in the main study as well as all staff members of the participating practices will be included (estimated n = 2,000). To ensure sufficient thematic breadth regarding the research questions – while simultaneously aiming for thematic saturation – a total of 4 practices will be included in the qualitative case studies, leading to about 60 individual interviews (30–60 minutes) with patients, relatives, and practice staff, along with approximately 16 qualitative activity logs. In addition, 4–5 cross-site focus groups (approximately 120 minutes each) with members of the PRIMA teams and stakeholders at interface levels (e.g., care support centers) are planned.

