### Control group – patients and practices

The CG consists of matched patients receiving usual care in comparable general practices outside the PRIMA intervention. Patients will be identified using routine data from the KVBW and AOK Baden-Württemberg (AOK BW) databases and matched to participants in the IG at both patient and practice level. Matching criteria include demographic and clinical characteristics such as age, sex, diagnosis, and comorbidities to ensure comparability between groups. Usual care reflects standard ambulatory primary care within the German statutory healthcare system as delivered by GPs outside the PRIMA intervention. This allows a pragmatic and policy-relevant evaluation of the intervention under real-world conditions, assessing the added value of the PRIMA care model compared to standard practice without altering routine care pathways. There is no control group for the PE.

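### The stated 82% power for a 15% reduction does not follow from the printed inputs, which give about 36% to 47% with the stated ICC

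*Protocol article*

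**What the plan says.** Under Sample size calculation, the protocol article states that "a baseline rate of 0.20 ASE per patient per year is assumed" and that "a conservative effect size of 15% is applied". On size it says: "The study follows a parallel cluster design with 20 practices per arm and approximately 112 patients per practice". On attrition: "This accounts for an anticipated dropout of 20% at practice level and 10% at patient level". It adds 12 months of observation before and after the start of the intervention (with a literature citation), an ICC of 0.01 and a two-sided alpha of 5%. From these it concludes that "the study achieves a statistical power of 82% to detect a 15% reduction in ASE rates".

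The section gives no variance for the count, no within-patient correlation between the two years and no correlation of practice effects between the two periods. It does not say whether 20 x 112 is before or after dropout. Outcomes (text and Table 2) defines the primary endpoint as a number of ASE over 12 months, which is a count. On practices, the Design section says: "The intervention group (IG) consists of the patients recruited from the 20 participating GP practices".

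**The concern.** The power statement is tied explicitly to the listed assumptions, so a reader should be able to recover it from them to within rounding. A rate of 0.20 with about 2,240 patients per arm yields only some 830 events in total, which is few for a 15% difference even before clustering is allowed for.

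The stake is interpretation. If the printed inputs hold and the true reduction is 15%, the trial is more likely to miss it than to find it. A non-significant result set against a stated power of 82% would look like stronger evidence against the care model than it is.

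**Working it through.** **Inputs** (all from Sample size calculation): control rate 0.20; intervention rate 0.20 x 0.85 = 0.17; k = 20 practices per arm; m = 112; n = 2,240 per arm; ICC 0.01; two-sided 5% (critical value 1.96). The effect on the log scale is |ln 0.85| = 0.1625. Power = Φ(0.1625/SE − 1.96). A power of 82% needs SE = 0.1625/(1.96 + 0.915) = 0.0565.

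**1. Count, no clustering, Poisson variance.** Expected events: 2,240 x 0.20 = 448 and 2,240 x 0.17 = 380.8. SE = √(1/448 + 1/380.8) = 0.0697; z = 2.33; power 64%.

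**2. With the stated ICC, post-period only.** Design effect = 1 + 111 x 0.01 = 2.11. SE = 0.0697 x √2.11 = 0.1012; z = 1.61; power 36%.

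**3. With baseline adjustment.** The variance is multiplied by 1 − r², where r = [m x ICC x CAC + (1 − ICC) x IAC] / [1 + (m − 1) x ICC]. CAC is the correlation of practice effects between periods and IAC the within-patient correlation. The document states neither. I take IAC = 0.
- CAC = 0.8: r = 0.896/2.11 = 0.425; SE = 0.0917; power 43%.
- CAC = 1.0: r = 1.12/2.11 = 0.531; SE = 0.0858; power 47%.

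**4. If 20 x 112 is before dropout.** 16 practices x 100.8 patients = 1,613 per arm; design effect 1 + 99.8 x 0.01 = 2.00. Power is 51% unclustered, 29% clustered, and 33% (CAC 0.8) to 37% (CAC 1.0) adjusted.

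**5. ASE read as yes/no, 20% v 17%, 20 x 112.** Power is 73% unclustered, 43% with the ICC, and 56% adjusted with CAC = 1.0.

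**6. Other readings that keep the ICC (20 x 112 unless stated).**
- One-sided test: 48.5% (count) or 55% (yes/no).
- ICC read as a squared coefficient of variation: 56.5%.
- 24 months of person-time: 45% to 62%.
- Difference-in-differences: 38%.
- 25 x 112 or 25 x 124.4: 43% to 53%.

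The only printed-input variant near the stated figure is 82.4%. It needs 25 practices per arm, a yes/no endpoint and no clustering, which contradicts the 20 practices, the count endpoint and the stated ICC.

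**7. What does reach 82%.** In the formula of step 3 with CAC = 1.0, it takes IAC of about 0.64 with Poisson variance: r = (1.12 + 0.99 x 0.64)/2.11 = 0.831; 1 − r² = 0.309; SE = 0.1012 x √0.309 = 0.0563. With yes/no variance it takes about 0.54.
- For a count, the first combination is inconsistent. If patients have stable individual rates, variance is mean x (1 + φ) and the year-to-year correlation is φ/(1 + φ). A correlation of 0.64 means φ = 1.78, so the variance is 2.78 times Poisson. Putting that in: SE = 0.1012 x √(2.78 x 0.309) = 0.0938; power about 41%.
- A yes/no correlation of 0.54 at a constant 20% means that 0.20 + 0.54 x 0.80 = 63% of patients with an ASE in one year have one in the next.

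**8. Reduction detectable with 82% power at 20 x 112.** About 26% post-only, 24% adjusted with CAC 0.8 and 22% adjusted with CAC 1.0.

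**The case against.** The strongest defence is that part of the calculation is not visible. The article condenses a fuller document, cites a source for the pre/post design, and may have used a repeated-measures method with correlations it does not print. Prior ASE or hospitalisation is one route into the trial (Table 1), and pre-period ASE is a matching variable (Matching), so some within-patient correlation is to be expected. This stands as far as it goes. A reader might infer that 82% is a plain arithmetic slip, or that 64% is an absolute ceiling. The document supports neither: 64% limits only the count reading, the yes/no reading gives 73% unclustered, and unreported inputs may lie behind 82%. What does not stand is 82% as a consequence of the printed assumptions, and the correlation needed is implausible for this count.

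A reader might also take 36% or 43% to 47% as the trial's true power. Those figures rest on Poisson variance and on correlations that I assumed; overdispersion would lower them. Nor is the 29% to 37% range established. The process evaluation expects about 2,000 people, patients and staff together, which is below 2,240 and leans towards 112 being a pre-dropout number, but the text does not settle it.

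Finally, the protocol calls 15% conservative against published reductions of 20% to 40%. On the same model, a true 25% reduction would have about 78% power post-only and 86% to 90% adjusted. The shortfall therefore concerns the 15% claim. It does not show that the trial cannot detect a larger effect, and it does not bias the estimate.

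**Conclusion.** The point holds as an error in the stated power. At 20 x 112 per arm, the printed inputs give about 64% for the count without clustering, 36% with the stated ICC, and 43% to 47% with pre-period adjustment. With clustering counted, the gap to 82% is 35 to 46 percentage points, far beyond rounding or choice of formula. If dropout still has to come off, the clustered figures are about 29% and 33% to 37%. The adjusted figures assume a between-period practice correlation of 0.8 to 1.0 and no extra within-patient correlation. The yes/no reading (73%, 43%, 56%) does not rescue the claim. The stated figure can be recovered only by adding inputs that are not reported and that do not fit a count with mean 0.20.

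**What to change.** Recompute and restate the power for the count endpoint. Name the method and report the count variance (Poisson or overdispersed), the within-patient correlation, the between-period correlation of practice effects, and whether 20 x 112 is before or after dropout. If further inputs produced 82%, print and justify them. Alternatively, state the reduction detectable with 82% power: about 22% to 26% at 20 x 112 under the assumptions above. The cost is one rewritten paragraph and a less favourable figure. No extra enrolment is needed.

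Optional, not required: the control group is drawn from claims data ("Patients will be identified using routine data from the KVBW and AOK Baden-Württemberg (AOK BW) databases"), so several matched control patients and practices per intervention unit could be used. With 3 to 5 times as many controls and the same 20 intervention practices, SE = √[(1/(c x 448) + 1/380.8) x 2.11] for c = 3 to 5. Power is then about 49% to 52% post-only, or 57% to 66% adjusted (CAC 0.8 to 1.0). That still falls short of 82%. It costs a larger extract, to be justified under the data-minimisation commitment, and possibly looser matches.
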